### Trial design {8}

MEMOIR is a fully decentralized, 2 × 2 full-factorial, randomized trial with four parallel groups allocated at a 1:1:1:1 ratio to (i) memantine and graded motor imagery; (ii) memantine only; (iii) placebo and graded motor imagery; and (iv) placebo only. All outcomes for each main comparison (memantine versus placebo; graded motor imagery versus no graded motor imagery) are tested for superiority. A 2 × 2 factorial design was chosen because there is little reason to expect an interaction between interventions (that is, there is little reason to expect the effects of either intervention, expressed as an absolute difference, depend on the presence or absence of the other intervention). In the absence of an interaction between interventions, a factorial design provides an efficient way to evaluate the effects of two interventions. This protocol and statistical analysis plan is reported in accordance with the Standard Protocol Items: Recommendations for Interventional Trials (SPIRIT) statement and the extension for factorial randomized trials [28–30].

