### Sample size {14}

The sample size calculation was based on a factorial analysis, where interventions are assumed to have independent effects. For the primary outcome of pain intensity at 16 weeks, we will be guided by a between-group difference of 1 point on an 11-point NRS to justify implementation of the interventions as suggested for chronic pain RCTs [55]. For the primary outcome of pain interference at 16 weeks, we will be guided by a between-group difference *T*-score metric of 5 to justify implementation of the interventions.

Using a repeated measures model with outcomes measured at baseline and follow-up timepoints, and with a correlation between adjacent time points of 0.7 [56], 182 participants are required to provide 90% power with a two-sided 2.5% significance level to detect an effect (of memantine compared to placebo, or graded motor imagery compared to no graded motor imagery) of either 1 point on an 11-point NRS for pain intensity, assuming a standard deviation of 2, or 5 *T*-metric points on the PROMIS Pain Interference scale, assuming a standard deviation of 10. Allowing for 10% dropout, we will aim to recruit a total of 204 participants (rounded up from 200.2).

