### Statistical methods for primary and secondary outcomes {20a}

#### Main analysis

All outcomes will be analysed according to the intention to treat principle. The analysis will involve estimation of the marginal mean effect of memantine compared to placebo and the marginal mean effect of graded motor imagery compared to no graded motor imagery on pain intensity and pain interference at 16 weeks. Additional information on the estimands of interest, including handling of intercurrent events, is provided in Table 2. As the trial has dual primary outcomes, interval estimates will be 97.5% confidence intervals. There will be no multiplicity adjustment for the two interventions as the factorial design answers two distinct questions.

**Table 2 Tab2:** Trial estimands

Estimand component	Definition
Interventions to be compared	To estimate the average causal effect of memantine, we will compare the mean outcome of trial participants allocated to receive memantine and graded motor imagery or memantine only with the mean outcome of trial participants allocated to receive placebo and graded motor imagery or placebo only To estimate the average causal effect of graded motor imagery, we will compare the mean outcome of trial participants allocated to receive memantine and graded motor imagery or placebo and graded motor imagery with the mean outcome of participants allocated to receive memantine only or placebo only
Population of interest	Adults with CRPS as defined by the trial eligibility criteria
Outcome of interest	Pain intensity, measured on a 11-point NRS; pain interference, measured with PROMIS pain interference v1.1
Summary measure (population-level)	Mean difference
Intercurrent events	All intercurrent events relating to memantine and graded motor imagery (e.g. intervention discontinuation, use of non-trial treatments) will be handled using a treatment policy strategy

For each of the dual primary outcomes, we will fit a longitudinal mixed-effects model that includes terms for the fixed effects of each intervention, the three follow-up timepoints, the intervention by time interactions, the two-way interaction between the interventions, and the baseline values of the outcome variables. In addition, the models will include terms for the fixed effects of the duration of CRPS (modelled as linear or linear with log transformation) and workplace compensation status, as well as random intercepts for trial participants.

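### If within-person correlation decays over time, the random-intercept model with a single baseline slope makes the week-16 interval wider than needed and the week-52 interval too narrow

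*Protocol article*

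**What the plan says.** The Main analysis section (Protocol article, {20a}) lists the terms of the model for each primary outcome: the two interventions, three follow-up times, intervention-by-time interactions, the interaction between the interventions, baseline values, CRPS duration "and workplace compensation status, as well as random intercepts for trial participants". It lists no baseline-by-time term, residual covariance structure, visit-specific variance or robust standard error. The week-16 marginal effects and their 97.5% intervals come from this model's coefficients and variance-covariance matrix, and secondary outcomes are handled the same way.

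The Sample size section {14} describes its basis as follows: "Using a repeated measures model with outcomes measured at baseline and follow-up timepoints", "with a correlation between adjacent time points of 0.7". It concludes that "182 participants are required to provide 90% power with a two-sided 2.5% significance level to detect an effect", with the pain effect given as "1 point on an 11-point NRS for pain intensity, assuming a standard deviation of 2". It names no correlation structure beyond the word adjacent.

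General analysis principles puts interpretation on point estimates and confidence intervals and rules out claims about significance. Trial status says that the article includes the statistical analysis plan.

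**The concern.** A random intercept as the only source of within-person dependence implies compound symmetry: one variance and one correlation for every pair of follow-ups. A single baseline term adds one slope for all visits. If baseline predicts week 16 better than week 52, the true residual variance is smallest at week 16 and largest at week 52, yet the model pools them. The primary interval then loses precision, and the interval for the sustained effect at week 52, a stated secondary objective, covers less often than its nominal 97.5%. In a trial that reads its results from interval estimates, width and coverage are part of the result.

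**Working it through.** **Inputs.** From Sample size {14}: SD 2, effect 1 point (standardised 0.5), 182 evaluable, two-sided 2.5%, 90% power, adjacent correlation 0.7. From Trial design {8}: "four parallel groups allocated at a 1:1:1:1 ratio", so each marginal comparison is 1:1. Equal SD at every visit is an assumption, because the plan gives one SD per outcome.

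**Step 1: the plan's own 182.** With baseline adjustment, total N = 4(z₀.₉₈₇₅ + z₀.₉₀)² v / 0.5², where v = 1 − r² and r is the correlation of baseline with the analysed visit. Here (2.2414 + 1.2816)² = 12.41, and 4 × 12.41 / 0.25 = 198.6, so N = 198.6 v, rounded up to equal arms.

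| Assumption | r | v | N (normal) | N (noncentral t) |
|---|---|---|---|---|
| Exchangeable 0.7, any visit; or the first follow-up | 0.700 | 0.510 | 102 | 104 |
| AR(1) by visit, third follow-up | 0.343 | 0.882 | 176 | 178 |
| AR(1) in time, 0.7 per 16 weeks, week 52 | 0.7^(52/16) = 0.314 | 0.902 | 180 | 182 |

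Of the variants tried for this baseline-adjusted contrast, only decaying correlation with a last-visit contrast came close to 182.

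**Step 2: what the specified model reports under AR(1) 0.7 by visit.** Baseline correlations are 0.70, 0.49 and 0.343. The common slope is their mean: b = 1.533 / 3 = 0.511. The actual residual variance factor at each visit is 1 − 2br + b²:
- week 16: 1 − 0.7154 + 0.2611 = 0.546
- week 26: 1 − 0.5008 + 0.2611 = 0.760
- week 52: 1 − 0.3505 + 0.2611 = 0.911

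The model uses their mean, 0.739, at every visit. With visit-specific slopes the factors are 1 − r² = 0.510, 0.760 and 0.882.

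**Step 3: standard errors and intervals.** SE = 2√(4v/182); half-width = 2.2414 × SE; coverage = 2Φ(2.2414 × model SE / actual SE) − 1.

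| Week | Model SE | Actual SE | Ratio | Coverage of 97.5% interval | Model half-width | Unstructured half-width |
|---|---|---|---|---|---|---|
| 16 | 0.255 | 0.219 | 1.16 | 99.1% | 0.571 | 0.475 |
| 26 | 0.255 | 0.259 | 0.99 | 97.3% | 0.571 | 0.579 |
| 52 | 0.255 | 0.283 | 0.90 | 95.7% | 0.571 | 0.624 |

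At week 16, 0.571 / 0.475 = 1.20. Power for 1 point at week 16 is Φ((1 − 0.571) / 0.219) = 97.5% under the specified model and 99.3% under the unstructured one.

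**Step 4: simulation.** 400 REML fits of the model as written (N = 184) gave empirical SEs of 0.217, 0.272 and 0.294 against a model SE of 0.253 at every visit. Coverage was 99.5%, 95.5% and 94.5%, with Monte Carlo error of about one percentage point at the later visits (√(0.945 × 0.055 / 400) = 1.1%).

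**Step 5: dependence on the assumed structure** (model SE / actual SE).

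| Structure | Week 16 | Week 26 | Week 52 |
|---|---|---|---|
| AR(1) by visit | 1.16 | 0.99 | 0.90 |
| AR(1) in time, 0.7 per 16 weeks | 1.16 | 1.03 | 0.88 |
| AR(1) by visit, week 12 counted (r = 0.49, 0.343, 0.240) | 1.06 | 0.99 | 0.96 |
| AR(1) by visit, week-16 SD 20% larger | 1.01 | 1.05 | 0.95 |
| Exchangeable 0.7 | 1.00 | 1.00 | 1.00 |

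With week 12 counted, week-16 power under the specified model is 92.7%.

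**The case against.** A reader might infer that the analysis model contradicts the sample size. The document does not support that. It states one correlation, for adjacent times; AR(1) decay is an inference. The recovery of 182 favours that inference, since an exchangeable 0.7 would need only about 104. But it came from trying several variants, and the exact match uses a week-52 contrast while the section frames its effects at week 16. A planning correlation also does not bind the analysis model. This objection stands, and it makes every figure conditional.

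The size is also sensitive. The Outcomes section has both primary outcomes measured at week 12 as well, and counting that visit cuts the misfit to about 6% and 4-5%. Unequal SDs can shrink it too, though AR(1) in time is slightly worse at week 52.

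The anti-conservative error falls on a secondary time point, coverage there is still near 95%, and the plan makes no significance decisions. That limits severity, but an interval labelled 97.5% should cover at about that rate.

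Finally, the planned blinded preliminary analysis is meant to settle distributional assumptions and could take in a covariance check. The section does not mention covariance, however, and the article says it contains the analysis plan, so the listed terms are fair to review.

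**Conclusion.** The point holds as a conditional improvement in precision and coverage. Under AR(1) 0.7 by visit, equal SDs and 182 evaluable participants, the week-16 interval carries about 0.1 NRS points of avoidable half-width (0.571 − 0.475), and the week-52 interval covers about 95.7% instead of 97.5%. The loss is smaller under milder decay and nil under exchangeable correlation.

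It would be wrong to conclude that the primary analysis is invalid or the trial underpowered. The effect estimates are unbiased, the week-16 interval errs on the conservative side, and week-16 power exceeds 90% under both AR(1)-by-visit readings and the exchangeable one. The case for change is that an unstructured covariance is valid whichever pattern is true, whereas the listed model gives correct visit-specific standard errors only when the residual variance is the same at all three visits.

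**What to change.** Before true allocations are used, prespecify for the continuous outcomes with repeated follow-up:

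- an unstructured residual covariance over weeks 16, 26 and 52 in place of the random intercept (in Stata, `residuals(unstructured, t(time))` with `noconstant`), fitted by REML with Kenward-Roger or Satterthwaite degrees of freedom;
- a baseline-by-time interaction;
- `margins` as planned for the week-specific marginal effects.

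The cost is one line of code, a sentence in the plan and about six parameters: six covariance terms instead of two, and two further baseline slopes, with about 200 participants. There is a small convergence risk, so name a fallback now, for example a simpler covariance structure with robust standard errors.

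Robust standard errors added to the current model would be a lesser fix. They would restore coverage and, in the AR(1)-by-visit case, give a week-16 half-width of 2.2414 × 0.219 = 0.49, still slightly above the 0.47 available. The planned blinded run on permuted allocations is the natural place to test the code.

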### Interim analyses {21b}

A formal interim analysis is not planned. The DSMB will use clinical expertise to perform an unblinded review of accruing safety data (adverse events and serious adverse events) at regular intervals and advise the Steering Committee whether the trial should be stopped for safety or ethical concerns.

### Methods for additional analyses (e.g. subgroup analyses) {20b}

#### Sensitivity analyses

Sensitivity analyses will be conducted to assess the impact of deviations to the ‘no interaction’ assumption on the primary outcomes. As recommended by Kahan et al. [59], the size, confidence intervals, and *p* value of the treatment-by-treatment interaction will be inspected to assess the plausibility of the assumption of no interaction underpinning the interpretation of the marginal estimator. Further sensitivity analyses will be conducted on the primary outcomes to estimate the effects of each intervention conditional on the presence or absence of the other intervention, again using the -margins- command in Stata. The effect of each intervention combination (memantine and graded motor imagery; memantine only; graded motor imagery and placebo) compared with the double control group (placebo only) will also be estimated (Supplementary Table 6). Multi-arm analyses remain unbiased even when interventions interact [59].

The analyses described below may be reported in secondary publications.

#### Subgroup analyses

Effect modification will be assessed by adding the following variables (one at a time, along with their interactions with one intervention at all time points) to the main analysis model, for each of the dual primary outcomes:Sex (male/female)Workplace compensation status (yes/no)CRPS duration (months; continuous)Opioid use (yes/no)

#### Cost effectiveness analysis

A within-trial economic evaluation will be conducted to assess the cost-effectiveness of memantine compared with placebo and graded motor imagery compared with no graded motor imagery, from a health care and societal perspective. Health outcomes will include clinical endpoints and health-related quality of life measured using the PROMIS Global Health. Utility values will be derived using the PROMIS-Preference (PROPr) Scoring System, which maps PROMIS responses onto a preference-based utility scale [60]. These utility values will be used to estimate quality-adjusted life years (QALYs) gained. Health care resource use will be estimated using linked administration data (MBS and PBS data) and patient questionnaires to capture the cost of health care utilisation, medication use, and out-of-pocket costs. Results will be reported as the cost per QALY gained and uncertainty explored using non-parametric bootstrapping. Sensitivity analyses will be conducted, where feasible, to test the robustness of the results. If the trial does not demonstrate a statistically significant difference in effectiveness, alternative economic evaluation approaches will be considered. The economic evaluation will follow the Consolidated Health Economic Evaluation Reporting Standards (CHEERS) guideline [61].

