## Statistical methods

### General analysis principles

The primary objective of the trial is to estimate the effects of memantine compared to placebo memantine and graded motor imagery compared to no graded motor imagery on pain intensity and pain interference. Consequently, the focus of the analysis and the interpretation of the trial findings will be on the magnitude of point estimates of effects and the precision of those estimates, quantified with confidence intervals. The analysis will be supplemented by *p* values but not by claims about statistical significance or non-significance [57].

Preliminary, blinded analyses will be conducted before the final analysis. The preliminary analyses will be conducted using randomly permuted ‘dummy’ treatment allocations. These analyses will identify any issues with the analysis pipeline and enable decisions to be made about, for example, distributional assumptions, without knowledge of the implications of those decisions on the trial’s findings. Once those issues have been resolved and the statistical code has been finalised, the definitive analysis will be conducted using true allocations. Analyses will be performed using R and Stata software.

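### A non-significant effectiveness result may reopen the choice of economic method, which conflicts with the plan's own rule against significance claims

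*Protocol article*

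**What the plan says.** Two sections of the protocol article, both under Statistical methods, bear on this.

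- **General analysis principles.** Interpretation will rest on "the magnitude of point estimates of effects and the precision of those estimates, quantified with confidence intervals". P values are added, "but not by claims about statistical significance or non-significance". The same section has analysis decisions settled on dummy allocations, so that they are taken without knowing what they do to the findings.
- **Cost effectiveness analysis** (within Methods for additional analyses {20b}). The aim is to "assess the cost-effectiveness of memantine compared with placebo and graded motor imagery compared with no graded motor imagery". The method is fixed: "Results will be reported as the cost per QALY gained and uncertainty explored using non-parametric bootstrapping". Later in the paragraph comes the conditional sentence: "If the trial does not demonstrate a statistically significant difference in effectiveness, alternative economic evaluation approaches will be considered".

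On status, the last line of the Sensitivity analyses section says of what follows, which includes the economic evaluation: "The analyses described below may be reported in secondary publications". Cost effectiveness is also listed among the secondary outcomes.

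**The concern.** The conditional sentence cannot be applied without declaring the effectiveness result significant or not. The general principles say the trial will make no such declaration, and nothing in the article exempts the economic evaluation.

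The sentence also makes the choice of economic approach depend on the observed result. The alternatives are left open, so the choice would be made by people who already know how the effectiveness comparison came out. That is the situation which the dummy-allocation step is meant to prevent elsewhere in the analysis.

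Finally, the rule adds nothing that the planned method lacks. Bootstrapping costs and QALYs already shows how uncertain both are. Putting a significance test in front of it invites the reader to treat a non-significant difference as no difference. For interventions that the article presents as low-cost, an imprecise but favourable estimate is a case in which the cost-per-QALY result is wanted.

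**Working it through.** **The text, side by side.** The point rests on no stated figure, so the check is a comparison of the two sections.

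1. The condition in the cost effectiveness section is the absence of a statistically significant difference. To know whether it is met, someone must classify the result as significant or non-significant.
2. The general principles exclude claims of that kind. Their heading is general, and they stand in the same Statistical methods part as the economic section.
3. The consequence is that alternatives will be considered. This is discretionary and comes after the result, and the alternatives are not named. Discretion makes the dependence on the result less controlled; it does not remove it.
4. The commitments to conduct the evaluation for both comparisons and to report cost per QALY with bootstrapping carry no condition, and the later sentence does not cancel them.

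The conflict is therefore in the stated rule and is not a matter of missing detail.

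**How easily a non-significant result can arise (illustration only).** The inputs come from Sample size {14}: "182 participants are required to provide 90% power with a two-sided 2.5% significance level", for an effect of "1 point on an 11-point NRS for pain intensity, assuming a standard deviation of 2". The stated power is taken as given and is not tested here. One outcome and one comparison are considered.

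*Scaling from the stated power.* With two-sided alpha 0.025 and 90% power, the expected z statistic at 1 point is 2.241 + 1.282 = 3.523. At a true difference of d points:

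- power = Φ(3.523 × d − 2.241)
- d = 0.5: Φ(1.761 − 2.241) = Φ(−0.480) = 0.32, so 68% non-significant
- d = 0.75: Φ(2.642 − 2.241) = Φ(0.401) = 0.66, so 34% non-significant

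*Assuming a baseline-to-16-week correlation of 0.7.* The plan gives 0.7 for adjacent time points; applying it to baseline and week 16 is an assumption. With 91 per margin:

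- residual SD = 2 × √(1 − 0.7²) = 1.428
- SE = 1.428 × √(2/91) = 0.212
- d = 0.5: Φ(0.5/0.212 − 2.241) = Φ(0.12) = 0.55, so 45% non-significant. Using 204 × 0.9 = 183.6 analysed also gives 45%.

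| True difference (NRS points) | Non-significant, stated 90% power at 1 point | Non-significant, correlation 0.7 assumed, 182 analysed |
|---|---|---|
| 0 | 97.5% | 97.5% |
| 0.5 | 68% | 45% |
| 0.75 | 34% | 10% |
| 1 | 10% | 0.7% |

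The condition can thus be met often when there is a real benefit smaller than the 1-point guide value. The conflict between the sections does not depend on these figures.

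**The case against.** Four arguments stand on the other side.

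- **The economic analysis is not dropped.** A reader might infer that a non-significant result would cost an intervention its cost-per-QALY analysis, or that the method changes automatically. The text supports neither. The evaluation and its reporting format are promised without condition, and alternatives are only to be considered. They could even be added beside the planned analysis. This stands in full and limits the point to what could happen.
- **The principle may be narrower than its heading.** The section opens from the primary objective and draws its estimation rule from that. It could be read as governing how the pain outcomes are interpreted, not which secondary analysis is run. This softens the conflict but does not remove it: the trigger is itself a verdict on effectiveness, and no exemption is stated.
- **Detail may sit elsewhere.** Which outcome, comparison, time point and alpha define the trigger, and what the alternatives are, could be left to a fuller economic plan. This stands, so the absence of those details is not part of the point. The significance-based condition is a different matter, because it is stated here.
- **The percentages do not measure the problem.** A reader might take 68% or 45% as the chance that the economic method changes. They are not that. They describe a single test on the pain scale, whereas effectiveness could also mean pain interference or QALYs. If both primary outcomes truly improved by half their guide values and were treated as independent (an assumption), with 182 analysed and an assumed correlation between 0 and 0.7, both would be non-significant in 51% to 21% of trials, and at least one in 92% to 70%. A non-significant result also need not lead to a change.

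**Conclusion.** The point holds in a limited form. The cost effectiveness section conditions its approach on a significance verdict that the general principles say the trial will not make, and it leaves room to choose the economic method after the result is known. The cost-per-QALY analysis remains planned, but it could be replaced or de-emphasised on the strength of a p value when the bootstrap already expresses the relevant uncertainty.

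The size is minor. The evaluation is an additional analysis that may be published separately, and the primary estimands, alpha, sample size and clinical conclusions are unaffected. The conclusion rests on reading the general principles as covering all analyses under Statistical methods, which their heading supports and nothing in the article contradicts. The percentages rest on the stated power or on the assumed correlation, and serve only to show that the condition is not a remote one.

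**What to change.** Delete the conditional sentence from the cost effectiveness section. In its place, state that the cost-utility analysis, with bootstrapped joint uncertainty in incremental costs and incremental QALYs, will be reported for memantine versus placebo and for graded motor imagery versus none, whatever the p values for effectiveness.

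If an alternative approach is to be kept, name it in advance, present it as an addition to the planned analysis, and give it a trigger that does not rest on significance. How the bootstrap output is displayed can be left to the authors.

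The cost is one sentence deleted and one or two added. No new data or methods are needed, since the bootstrap is already planned. According to Trial status, all outcomes are analysed together after the last 52-week follow-up, with the final assessment anticipated in Q2 2027, so the change can be made before any results are known.
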